### Power and sample size calculations

Data obtained from a random sample of black participants recruited from the MetSO Cohort Study has provided a current estimate of the rate of comprehensive assessment of sleep apnea to be expected in the proposed study. Analysis of the data suggested that 47% of participants referred for sleep assessment would adhere to physician recommendations after exposure to TTI, whereas 35% of those in a control group agreed to undergo a sleep assessment. Thus, this represents the likely rate of adherence expected in our AC group. We propose to achieve an adherence rate of 47% among participants exposed to the TTI.

With an expected 12% increase in the adherence rate associated with the TTI, a standard error of 0.10%, and a sample size of 340, the study will be adequately powered (90%) to detect significant increase in the outcome measures using chi-square tests. The primary study outcome in this project is documented receipt of a sleep apnea assessment. A two-tailed test, with alpha = 0.05, comparing adherence rates of 35% with 47% requires 170 participants per group [42]. The precision estimated in that analysis is the approximate expected precision of study data. Specifically, a difference of 12% would be observed at chi-square = 21.03 with a 95.0% confidence interval of 3% to 20%. With the proposed sample size, the study will have 85% power to achieve a one-standard deviation increase in the odds ratio of adherence attributable to proposed mediators: sleep apnea knowledge, self-efficacy, readiness, and trust/rapport with the HE (expressed as continuous variables).

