### Chart audit

Upon completion of a sleep assessment, a participant’s chart (intervention or attention control) will be subjected to a random audit. Audits for confirming self-report will be conducted by one of the study investigators, who will be blinded to randomization status. Verification of a sleep assessment entails documentation of an appropriate sleep history and a polysomnographic study.

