### Statistical analysis

To describe the characteristics of the study population, we will use measures of central tendencies and dispersion for continuous data; frequency distributions will be used for categorical data. Chi-square tests will be used to compare categorical data, and ANOVA will be used for continuous data. Relationships between mediators of adherence to recommended sleep apnea assessment and CPAP treatment will be examined using binary multivariate logistic regression analysis. The two main dependent measures will be: adherence to physician-recommended sleep assessment (yes versus no) and adherence to CPAP treatment (yes versus no). Candidate mediators will include sleep apnea knowledge, self-efficacy, readiness, and trust/rapport with the HE. Effects of sociodemographic and clinical factors will be adjusted in those analyses. Repeated-measures MANCOVA will be used to examine differences between baseline and follow-up measures (for example, waist circumference (WC), BP, HDL-C, FBG/HbA1c); age, sex, and sleepiness will be entered as covariates. MANCOVA is a robust technique that incorporates routines to account for heterogeneous variances, serial correlations, and variance inflation [41].

### Hypothesis 1

TTI will lead to higher rates of sleep apnea assessment at 6 months. A comprehensive assessment of sleep apnea will be defined by documentation of an appropriate medical and sleep history by a sleep clinician and a nocturnal polysomnographic study.

#### Analysis for hypothesis 1

Analysis will be performed on an intention-to-treat basis. All participants in the treatment arm will be assumed to have received the full dose of the telephone intervention and all participants in the attention-control arm will be assumed to have received no tailored intervention. Prior to testing for intervention effects, we will verify the comparability of the treatment and control arms with respect to all available demographic and personal data. T-tests and chi-square tests will be used for continuous and categorical variables, respectively. Thus, receipt of sleep apnea assessments within the 6-month period will be a binary outcome, yes or no. We will use logistic regression to estimate the odds associated with receipt of sleep apnea assessment contrasting the two study arms.

### Hypothesis 2

TTI will lead to higher adherence rates to recommended follow-up care (that is, CPAP use (> 4 hours a night for 70% of the nights)) post-diagnosis of sleep apnea.

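### The planning rates in the power section are not described for one and the same event, so at least the 35% control rate is not shown to be a rate of the documented-receipt endpoint

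*Protocol article*

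**What the plan says.** Four descriptions bear on the planning rates. All but the endpoint's detailed definition stand in the Power and sample size calculations section of the protocol article.

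- **Pilot data as a whole:** a random sample from the registry cohort "has provided a current estimate of the rate of comprehensive assessment of sleep apnea to be expected in the proposed study".
- **Telephone-intervention rate:** "47% of participants referred for sleep assessment would adhere to physician recommendations after exposure to TTI". The section then also presents 47% as the rate the trial proposes to reach.
- **Control rate:** "whereas 35% of those in a control group agreed to undergo a sleep assessment". The next sentence reads: "Thus, this represents the likely rate of adherence expected in our AC group".
- **Endpoint being powered:** "The primary study outcome in this project is documented receipt of a sleep apnea assessment". Under Hypothesis 1 in the Statistical analysis section, a comprehensive assessment is "defined by documentation of an appropriate medical and sleep history by a sleep clinician and a nocturnal polysomnographic study", and receipt is a yes/no outcome over 6 months. The Chart audit section agrees: "Verification of a sleep assessment entails documentation of an appropriate sleep history and a polysomnographic study".

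On these rates the section claims 90% power with 340 participants, 170 per group, by a two-tailed chi-square test at alpha 0.05.

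**The concern.** Agreeing to an assessment is an intention. The endpoint is a completed and documented procedure with two components. The article moves from one to the other without giving a conversion.

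The protocol itself treats the two as different events. The Phase I section has the health educator record a verbal commitment, check the next day whether the appointment was kept, and work through obstacles if it was not. The Follow-up procedures section makes the first sleep-center visit a consultation, so a kept first visit need not yet include polysomnography.

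The two rates also differ in wording: one is agreement, the other is adherence. If they count different events, the 12-point difference is not a like-for-like effect. A power statement is only as good as the match between its input proportions and the endpoint, and here a reader cannot tell whether they match.

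**Working it through.** **Inputs from the article.** Control 35%, telephone intervention 47%, 170 per arm, two-sided alpha 0.05 (Power and sample size calculations); 1:1 allocation (Design and methods). **Assumed input.** The fraction c of those who agree and go on to documented completion. The article gives no value, so c runs from 1.0 down to 0.6.

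**Formula.** With p̄ = (p1 + p2)/2 and n per arm:

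power = Φ{ [ |p2 − p1| − 1.96·√(2p̄(1 − p̄)/n) ] / √( [p1(1 − p1) + p2(1 − p2)]/n ) }

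**Step 1: the plan's own figure.** p̄ = 0.41. The null standard error is √(2 × 0.41 × 0.59/170) = 0.0533, and 1.96 times that is 0.1046. The alternative standard error is √((0.2275 + 0.2491)/170) = 0.0529. Power = Φ((0.12 − 0.1046)/0.0529) = Φ(0.29) = 61.5%. The stated 90% is not reproduced. Other methods do not rescue it: arcsine 61.6%, unpooled 62.0%, continuity-corrected 57.2%, one-sided 72.9%. Two-sided 90% power needs 351 per arm. This shortfall exists even if both rates are accepted as completion rates, so it is not a consequence of the wording problem.

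**Step 2: what each figure is said to count.**

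| Figure | Event described |
|---|---|
| Pilot data overall | comprehensive assessment |
| 35% | agreement to an assessment |
| 47% | adherence to medical advice, then a target |
| Endpoint | documented clinician history plus polysomnography within 6 months |

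Only the 35% is worded as agreement. The opening sentence of the section points the other way, because comprehensive assessment is the term that Hypothesis 1 defines as the endpoint.

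**Step 3: what the ambiguity could do to power.** The control rate becomes 35% × c. The intervention rate depends on the reading: 47% × c (both rates are agreement rates); the planned odds ratio held, (0.47/0.53)/(0.35/0.65) = 1.65; the 12-point difference held; or 47% held (only the control rate is agreement). Each cell gives the intervention rate and the power at 170 per arm.

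| c | Control | Both shrink | Odds ratio held | 12 points held | Only control shrinks |
|---|---|---|---|---|---|
| 1.0 | 35.0% | 47.0%: 61.5% | 47.0%: 61.5% | 47.0%: 61.5% | 47.0%: 61.5% |
| 0.9 | 31.5% | 42.3%: 54.1% | 43.1%: 60.0% | 43.5%: 62.8% | 47.0%: 83.6% |
| 0.8 | 28.0% | 37.6%: 47.0% | 39.0%: 57.8% | 40.0%: 64.8% | 47.0%: 95.5% |
| 0.7 | 24.5% | 32.9%: 40.2% | 34.8%: 55.0% | 36.5%: 67.2% | 47.0%: 99.3% |
| 0.6 | 21.0% | 28.2%: 33.7% | 30.4%: 51.3% | 33.0%: 70.4% | 47.0%: 99.9% |

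Worked cell (both shrink, c = 0.8): p̄ = 0.328; null standard error 0.0509; alternative standard error 0.0507; Φ((0.096 − 0.0998)/0.0507) = Φ(−0.075) = 47.0%.

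Power falls under two readings and rises under the other two.

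**The case against.** The best defence is that a single loose verb is being over-read. The section opens by calling the pilot figure a comprehensive-assessment rate, carries it on as an adherence rate, and later compares two adherence rates. On that reading both figures are completion rates and only the word for the control group is wrong. This is possible and cannot be excluded. It still leaves one number described in two incompatible ways, and that needs correcting whichever description is true.

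Three stronger readings are tempting, and the article supports none of them.

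- **The whole power statement is for another outcome.** Only the 35% is worded as agreement; the 47% is not.
- **35% is an upper bound for the control rate.** Completion is bounded by agreement only for the same people under the same contact and follow-up. Trial controls may receive up to 10 calls (Description of the attention-control arm) and are counted over 6 months. The article does not say what contact or follow-up the pilot controls had, and someone who first declined could complete later.
- **Power on the true endpoint must be lower.** The section fixes both a 47% target and a 12-point increase. If either is kept while the control rate falls, power rises.

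It can also be said that pilot numerators and denominators belong in the full protocol, and that is fair: their absence is not the point here. The point is an inconsistency in what is printed. The practical reach is limited, since 311 participants were already randomized (Trial status) and neither the endpoint definition nor the analysis is affected.

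**Conclusion.** The planning rates are described inconsistently. At least the control input, and possibly the 12-point contrast, is not shown to be for documented receipt of an assessment.

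Neither the direction nor the size of the effect on power can be settled from the article. Over an assumed completion fraction of 60% to 100%, with 170 per arm and two-sided 0.05, power runs from 34% to 61% if both rates shrink, 51% to 61% if the odds ratio of 1.65 is held, 61% to 70% if the 12-point difference is held, and 61% to above 99% if only the control rate shrinks. The common starting value of 61% assumes that 35% and 47% are both completion rates. No dropout allowance is applied.

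The gap between 61% and the stated 90% is a separate arithmetic fault and should not be attributed to the wording. It does mean that the power sentence has to be rewritten in any case.

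**What to change.** In the Power and sample size calculations section:

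1. Give both rates as documented receipt (clinician history plus polysomnography within 6 months), defined identically for the two arms. If the pilot recorded only agreement for either rate, say so.
2. In either case, restate power at 340 (170 per arm, two-sided 0.05): about 61% if 35% v 47% are accepted as completion rates.
3. If either rate is agreement only, show power over a stated completion fraction, for example 60% to 100%, under each of the four readings tabulated above, and mark the fraction as an assumption.

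The 35% should not be labelled an upper bound, the text should not say that power must fall, and the sample size should not change.

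The cost is a re-read of the pilot records and a revised paragraph. The downside is a less favourable or wider stated power.

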## Design and methods

This is a randomized controlled trial to examine the efficacy of a culturally and linguistically tailored behavioral telephone-delivered intervention to increase adherence to physician-recommended assessment and treatment of sleep apnea. Participants will be randomized either to a tailored-telephone intervention (TTI) arm or an attention-control (AC) arm. Approximately 340 black participants at risk for sleep apnea will be randomly assigned to one of the two treatment conditions (170 in each arm). Intervention content for the TTI will be delivered by a trained HE who has experience working with minority populations. The HE has a bachelor’s degree and will receive significant training in sleep medicine, including both basic theories and laboratory-based recording and treatment procedures. She will be supervised throughout the study period by the lead investigator. Assessments will be conducted at baseline, and at 6- and 12-months post-randomization. Participants will receive $10 at baseline and $100 at the 6-month follow-up.

The institutional review boards (IRBs) at SUNY Downstate Medical Center (protocol #09-193) and NYU Langone Medical Center (protocol #13-00182) approved this study prior to implementation.

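### The stated 90% power does not follow from the plan's own inputs: 170 per arm gives about 61% power for 35% versus 47%

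*Protocol article*

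**What the plan says.** Everything needed for the check is in the protocol article, mostly under Power and sample size calculations.

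- **Outcome:** "The primary study outcome in this project is documented receipt of a sleep apnea assessment". The analysis for hypothesis 1 makes this a yes/no outcome within 6 months.
- **Control rate:** "35% of those in a control group agreed to undergo a sleep assessment", taken as the rate expected in the attention-control arm.
- **Intervention rate:** "We propose to achieve an adherence rate of 47% among participants exposed to the TTI".
- **Test, alpha and size:** "A two-tailed test, with alpha = 0.05, comparing adherence rates of 35% with 47% requires 170 participants per group".
- **Power:** with "a sample size of 340, the study will be adequately powered (90%) to detect significant increase in the outcome measures using chi-square tests".

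Design and methods confirms 1:1 allocation with 170 in each arm, and Recruitment and screening gives 340 as the total. The power section also gives a standard error of 0.10%, a chi-square of 21.03 for a 12-point difference, and a 95% confidence interval of 3% to 20%.

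**The concern.** A 12-point difference between two mid-range proportions usually needs well over 170 per arm for 90% power, so the figure called for recalculation. This section is the only sample-size justification for the outcome that it calls primary.

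If the power is overstated, readers will weigh the result wrongly. A non-significant finding from a trial described as 90% powered invites the conclusion that the intervention does not produce a 12-point gain. That conclusion is much weaker if the design would miss such a gain nearly 40% of the time. The error does not bias the effect estimate or inflate the type I error. It misstates what the trial can show.

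**Working it through.** **Inputs (all from the protocol article).** p1 = 0.35, p2 = 0.47, difference d = 0.12, n = 170 per arm, two-sided alpha = 0.05 (z = 1.960), mean proportion 0.41.

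**1. Try to reproduce the stated 90%.** Pooled-variance formula for the chi-square test of two proportions:

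- SE under no difference: sqrt(2 × 0.41 × 0.59 / 170) = sqrt(0.4838 / 170) = 0.0533
- SE under the alternative: sqrt((0.35 × 0.65 + 0.47 × 0.53) / 170) = sqrt(0.4766 / 170) = 0.0529
- Power = Φ[(0.12 − 1.960 × 0.0533) / 0.0529] = Φ(0.29) = **0.615**

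The type II error is 38.5%. The stated figure is not reproduced.

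**2. Other ways of computing it at 170 per arm.**

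| Method | Power |
|---|---|
| Pooled variance, two-sided | 61.5% |
| Unpooled variance, two-sided | 62.0% |
| Arcsine, two-sided | 61.6% |
| Exact enumeration of the Pearson chi-square test | 62.5% |
| Continuity-corrected, two-sided | 57.2% |
| Pooled variance, one-sided 5% | 72.9% |

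**3. Sample size needed.** n per arm = [1.960 × sqrt(0.4838) + z_power × sqrt(0.4766)]² / 0.12²

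- 90% power (z = 1.2816): (1.3633 + 0.8848)² / 0.0144 = **351 per arm** (702 in total), or 368 per arm with continuity correction
- 80% power (z = 0.8416): (1.3633 + 0.5810)² / 0.0144 = **263 per arm**

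So 170 per group is not what 35% versus 47% requires at 80% power either.

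**4. What 170 per arm can detect.** With 35% in control, power reaches 80% at an intervention rate of about 50% (15 points) and 90% at about 52% (17 points).

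**5. Where 90% might have come from.** Two calculations land close to it: 340 *per arm* (89.1%), and a one-sample test of 170 participants against a fixed 35% (89.6%). Neither is the stated design. A control rate near 8% would also give about 89% for a 12-point difference, but the plan states 35%. The source of the error cannot be established from the document.

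**6. The accompanying precision figures.** With observed rates of 35% and 47% in 170 per arm:

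| Quantity | Stated | Recomputed |
|---|---|---|
| Standard error of the difference | 0.10% | 5.3 percentage points |
| Chi-square | 21.03 | 0.0144 / (0.4838 / 170) = 5.06 |
| 95% confidence interval | 3% to 20% | 12 ± 1.96 × 5.29, i.e. 1.6% to 22.4% |

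The stated values do not agree with each other. A chi-square of 21.03 implies 21.03 × 0.4838 / 0.0144 ≈ 707 per arm. A half-width of 8.5 points implies 1.96² × 0.4766 / 0.085² ≈ 253 per arm.

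**The case against.** The best defences look for something in the design that would recover the lost power.

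- **Pairing.** The Randomization section says allocation is carried out in pairs, so a matched analysis might be more efficient. To reach 90% with 170 pairs, the variance would have to fall to about 170/351 = 0.48 of its unpaired value, which needs a within-pair outcome correlation of about 0.5. The section describes no matching on prognostic factors, and the planned analyses are chi-square tests and logistic regression, not a matched-pair test.
- **Covariate adjustment.** It would have to remove about half the outcome variance, and the power claim is expressly for chi-square tests.
- **The cited reference.** It is not available, but the conflict lies entirely among figures printed in the section.

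None of these rescues the 90%. Three narrower points do stand:

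- The sentence stating "comparing adherence rates of 35% with 47% requires 170 participants per group" carries no power figure of its own. Linking it to 90% is an inference from the sentence before it, though a natural one.
- The 311 randomised under Trial status is a count to date, not the final size. Power at that number, about 58% if split evenly, is only context.
- How a null result would be read is a prediction, since the article gives no interpretation rule.

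**Conclusion.** The concern holds. For the stated comparison, power is about 61% (57% to 63% across two-sided methods) against 90% claimed, a shortfall of nearly 30 percentage points in the flattering direction. The chance of missing the design effect is about 38.5%, close to four times the 10% implied.

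This takes the plan's 35% and 47% as given and assumes complete outcome data on 340 participants. The section states no allowance for loss. Assumed losses of 10% to 20%, which are not figures from the document, would bring power to about 57% and 52%. Because this is the headline design property for the primary outcome, it must be corrected.

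**What to change.** Replace the power sentence, including its standard error of 0.10%, with wording such as:

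> With 170 participants per arm, a two-sided chi-square test at the 0.05 level has about 61% power for 35% versus 47%. With 35% in the control arm, it has 80% power for a difference of about 15 percentage points and 90% power for about 17.

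Then:

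- Delete the statement that comparing 35% with 47% requires 170 per group.
- Correct the precision sentence. Observed rates of 35% and 47% would give a chi-square of about 5.06, a standard error of about 5.3 points and a 95% confidence interval of about 1.6% to 22.4%. If these figures stay as they are, the section would still contradict itself.
- Add that a non-significant result will be interpreted from its confidence interval and not taken as showing no effect. This is a recommendation that follows from the lower power, not a correction of existing text, and it is most credible if written before analysis.

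The cost is wording only. Enrolment, conduct and analysis do not change. The price is a less favourable stated power.

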### Outcomes

The primary outcome will be adherence to physician-recommended assessment and treatment for sleep apnea. The secondary outcomes will include 1) maintenance of recommended treatment at 6 months and at 12 months; 2) waist circumference; 3) lipid levels; 4) BP; and 5) FPG or HbA1c for those who have a DM diagnosis. Outcomes assessment will be conducted at baseline, and at 6- and 12-months post-randomization.

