#### Analysis for hypothesis 2

The analysis plan is similar to that for hypothesis 1. The focus will be on adherence to recommended CPAP treatment. We will use logistic regression to estimate the likelihood of adhering to prescribed CPAP treatment after a diagnosis of sleep apnea was made.

### Hypothesis 3

Effects of the intervention in maintaining adherence will be sustained 6 months after active interventions and interventions will improve clinical outcome measures (WC, BP, HDL-C, and FPG/HbA1c).

#### Analysis for hypothesis 3

We will test the hypothesis that participants in the intervention arm will sustain gains from the initial interactions with the HE, leading to long-term adherence to recommended treatment and follow-up care. It is routinely recommended that participants with sleep apnea return for a follow-up visit after initiating treatments, during which adherence to treatment plan and improvement in sleep parameters is assessed. In our protocol, clinical outcomes (WC, BP, HDL-C, and FPG/HbA1c) will be ascertained post treatment. The analysis plan to test adherence at 6 months post-randomization is similar as for hypotheses 1 and 2; participants returning for a follow-up visit will be grouped as long-term adherents versus non-adherents. Chi-square tests and logistic regression analyses will be used. Repeated-measures MANCOVA will be employed to examine differences between baseline and post-intervention measures (WC, BP, HDL-C, and FPB/HbA1c). *Post hoc* comparisons between groups will be performed with Bonferroni corrections, where univariate results are significant. As required by assumptions governing the use of ANOVA, and since we expect the dependent variables to be modestly correlated, we will first examine their collinearity. Next, normality of the distribution of each measure will be examined and transformations will be performed for non-gaussian distributions. In exploratory analyses, we will determine whether mixed effect modeling would support ANOVA results.

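### The 90% power statement is worded to cover all the outcome measures, but the calculation behind it concerns receipt of a sleep assessment only and does not carry over to CPAP adherence

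*Protocol article*

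**What the plan says.** The section Power and sample size calculations begins its claim with "With an expected 12% increase in the adherence rate associated with the TTI, a standard error of 0.10%, and a sample size of 340" and concludes that "the study will be adequately powered (90%) to detect significant increase in the outcome measures using chi-square tests". It then states "The primary study outcome in this project is documented receipt of a sleep apnea assessment", and continues: "A two-tailed test, with alpha = 0.05, comparing adherence rates of 35% with 47% requires 170 participants per group". The 35% and 47% are introduced there as rates of undergoing a sleep assessment. The section gives no CPAP adherence rate, CPAP effect size or number expected to be diagnosed.

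Other sections describe the endpoints more broadly. Outcomes says "The primary outcome will be adherence to physician-recommended assessment and treatment for sleep apnea". Statistical analysis says "The two main dependent measures will be: adherence to physician-recommended sleep assessment (yes versus no) and adherence to CPAP treatment (yes versus no"). Hypothesis 2 concerns CPAP use following a diagnosis, and its analysis reads "We will use logistic regression to estimate the likelihood of adhering to prescribed CPAP treatment after a diagnosis of sleep apnea was made". The same paragraph calls that analysis similar to the one for hypothesis 1, which is by intention to treat.

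**The concern.** The power sentence speaks of outcome measures in the plural. A reader who has just read in Outcomes that treatment adherence belongs to the primary outcome will take the 90% to apply to CPAP adherence as well. The calculation does not support that. It compares assessment rates in all 340 participants, whereas the CPAP comparison is written for people who have been diagnosed, and diagnosis requires the assessment that fewer than half are expected to have.

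If the wording stands, the treatment half of the primary aim appears to have a power that the design has not been shown to have. A non-significant CPAP result could then be given more weight as evidence against the intervention than the sample allows.

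**Working it through.** **Inputs from the protocol article.** Two-sided alpha 0.05; 35% (control) versus 47% (intervention) for assessment; 340 participants, 170 per arm. No dropout is assumed, which favours the plan.

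**Formula.** Normal approximation for two independent proportions with pooled variance under the null:

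power = Φ[(d − 1.96·s0) / s1], where d = p2 − p1, s0 = √[p̄(1 − p̄)(1/n1 + 1/n2)] with p̄ the overall rate weighted by n1 and n2, and s1 = √[p1(1 − p1)/n1 + p2(1 − p2)/n2].

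**Step 1: the plan's own figure, for assessment.** With n = 170 per arm, d = 0.12, p̄ = 0.41, s0 = 0.0533 and s1 = 0.0529: (0.12 − 1.96 × 0.0533)/0.0529 = 0.29, so power is 61%. The stated 90% is not reproduced. It would need 351 per arm; 340 per arm, rather than in total, gives 89%. That is a separate error, and correcting it would not settle the CPAP question.

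**Step 2: expected number available for the CPAP comparison.** Expected assessed: 0.35 × 170 = 59.5 in control and 0.47 × 170 = 79.9 in the intervention arm, so about 60 and 80. Those diagnosed cannot outnumber those assessed.

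**Step 3: power for CPAP adherence at 60 versus 80.** The control CPAP rate and the 12-point CPAP gain are assumptions made here, because the article gives neither. At 35% versus 47%, p̄ = 0.419, s0 = 0.0843 and s1 = 0.0831: (0.12 − 1.96 × 0.0843)/0.0831 = −0.54, so power is 29%. Over other control rates:

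| Control | Intervention | Power |
|---|---|---|
| 10% | 22% | 46% |
| 20% | 32% | 35% |
| 35% | 47% | 29% |
| 50% | 62% | 29% |
| 60% | 72% | 32% |
| 80% | 92% | 55% |

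If only 70% of those assessed are diagnosed (an assumption; 42 versus 56), power at 35% versus 47% is 22%. With 60 versus 80, 90% power needs a gain of about 26 to 27 points (control rate of 50% or 35%).

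**Step 4: the alternative reading, all randomised.** Take 170 per arm and count the unassessed as non-adherent. Suppose half of those assessed in the control arm adhere; half is the general-population figure in Background, used here as an assumption. The control rate is then 0.35 × 0.50 = 17.5%.

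- Same adherence among the assessed in both arms: 0.47 × 0.50 = 23.5%. Power 28%.
- A 12-point gain among the assessed: 0.47 × 0.62 = 29.1%. Power 72%.
- A 20-point gain among the assessed: 0.47 × 0.70 = 32.9%. Power 91%.
- A lower base, 7% versus 19% (0.07/0.35 = 20% and 0.19/0.47 = 40% of the assessed). Power 91%.

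**The case against.** The strongest reply is that the sentence after the claim names receipt of an assessment as the primary study outcome, and that both planning rates are assessment rates. Read as a whole, the paragraph ties the 90% to assessment, and the plural is loose wording. That has force: it shows what the calculation was for and which way the sentence should be corrected. It does not remove the conflict with Outcomes, where treatment adherence is part of the primary outcome.

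A second reply is that the sentence on two main dependent measures stands among sentences about mediators, and may only name the dependent variables of those regressions. This is fair, and the point does not depend on it; Outcomes and hypothesis 2 are enough.

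A third is that the CPAP control rate and effect used above are not the plan's. That is true, so the power values are illustrations over a range. In particular, the half-adherent figure describes the general population, and Background says adherence among black patients is worse.

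A reader might infer that no reading can give CPAP adherence 90% power, or that 60 and 80 are hard limits. The documents support neither. Describing the hypothesis 2 analysis as similar to an intention-to-treat one leaves the all-randomised reading open, and Step 4 shows that large assumed gains then reach about 91%. The 60 and 80 are expected counts at the planning rates; actual uptake may differ.

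Finally, a condensed article may leave a full CPAP power analysis to a longer document. Its absence alone would be no finding; the finding is that the printed claim extends to an endpoint for which it was not calculated.

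**Conclusion.** The point holds as one of scope. The 90% statement is worded for all outcome measures, but it derives from assessment rates in 170 versus 170 and gives no support for CPAP adherence.

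On the post-diagnosis analysis as written, with a 12-point CPAP gain assumed, power is about 29% to 35% for control rates of 20% to 60%, and at most about 55% at the extreme rates tried. This already assumes that everyone assessed is diagnosed and that nobody drops out. On the all-randomised reading, power runs from about 28% to 72% for gains of zero to 12 points among the assessed, starting from half adherent; gains of about 20 points are needed for 90%.

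The article also has to settle whether the primary outcome is receipt of assessment alone, as the power section says, or assessment and treatment together, as Outcomes says.

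**What to change.** In Power and sample size calculations, replace the reference to outcome measures in general with receipt of a sleep apnea assessment, and make no 90% claim for CPAP adherence. Correct the 90% for assessment separately, since the stated inputs give about 61%.

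Add a line on CPAP adherence giving its expected denominator (about 60 control and 80 intervention participants, or fewer, if analysed after diagnosis) and its power as a range, with the assumed control rate and gain labelled as assumptions. If everyone randomised is to be analysed, say so and give the range for that analysis instead.

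Make Outcomes and the power section agree on the primary outcome. A statement that CPAP adherence will be reported as an estimate with a 95% confidence interval, and that a non-significant result will not be read as no effect, would help but is optional.

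These are wording changes and need no further participants or data. The downside is a less favourable printed power for CPAP adherence.
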